#### **(4) syncope**

It can occur due to anxiety or psychological and physical discomfort. Differentiating it from seizures is necessary. Generally, if consciousness is quickly regained within a few seconds, or if there are prodromal symptoms such as dizziness, pallor, bradycardia, or nausea, it is often considered a vasovagal response rather than a seizure. If a loss of consciousness occurs, TMS stimulation should be immediately stopped. Medical personnel should assess airway and pulse, and if consciousness does not return for more than 30 seconds, appropriate measures should be taken similar to treating a seizure.

#### **(5) transient hearling loss, tinnitus**

During rTMS stimulation, earplugs will be used, and in case of any symptoms arising, an immediate referral to an otolaryngologist (ENT specialist) will be arranged. Participants with cochlear implants, history of significant noise exposure, or prior use of ototoxic medications will be excluded from the clinical trial.

Table. Reported side effects in high frequency rTMS [14]

| Side effects                                    | Frequency                                                                      |
|-------------------------------------------------|--------------------------------------------------------------------------------|
| Seizure                                         | In patients with epilepsy~ 1.4%
In health individuals<1%                    |
| Transient acute hypomania induction             | Possible occurrences during left prefrontal cortex stimulation.                |
| syncope                                         | Often appears due to psychological reasons rather than direct effects of rTMS. |
| Headache, localized pain, neck pain, parathesia | Frequent                                                                       |
| Transient hearing loss                          | Possible                                                                       |
| Burns                                           | Occasionally reported                                                          |

## 11.2 Electroencephalography (EEG)

There is no known risk associated with the EEG device currently used for diagnostic purposes at Samsung Medical Center.

## 11.3 MRI (structural MRI, resting fMRI)

There is no known risk associated with the device currently used for diagnostic purposes at Samsung Seoul Hospital, which is also known to be safe from causing claustrophobia or contrast agent-related side effects.

When anticipated side effects occur, they will be categorized into three levels based on their severity. The investigator will record the name of the side effect and its severity level in the case report form.

## **12. Termination or Withdrawal Criteria and Re-screening**

### **12.1 Criteria for Study Termination and Handling Study Termination**

#### **12.1.1 Criteria for Study Termination**

If serious adverse events occur during follow-up, these results will be discussed immediately by the clinical trial committee, and if the results are deemed sufficiently conclusive to justify termination of the study, the trial will be halted.

- If seizures or skin reactions occur during stimulation and the investigator deems it necessary to stop the stimulation, the trial will be halted.
- If the investigator deems it best for the participant to stop for any reason at any time, the trial will be halted.

Deviation from the protocol will not result in discontinuation of participants unless it poses a significant risk to their safety. Participants have the right to withdraw from the clinical trial voluntarily at any time. Participants who express the intention to discontinue their participation, fail to attend visits, or fail in follow-up observations for any reason may be considered as termination.

#### **12.1.2 Handling of Study Termination**

Interventions or treatments will be administered to discontinued participants as necessary, and their progress will continue to be observed.

All test results, the date of discontinuation, reasons for discontinuation, subsequent interventions, and progress after discontinuation will be documented in the case report form

In case the clinical trial is terminated, the Clinical Trial Investigator will notify the Institutional Review Board (IRB) in writing about the termination along with the reasons for termination.

### **12.2 Criteria for Withdrawal and Handling of Withdrawal**

#### **12.2.1 Criteria of Withdrawal**

- 1) Patient's Request: Any patient who wishes to withdraw from the study can do so, but they will receive counseling from the medical staff about the need for long-term follow-up observation.
- 2) Serious, unexpected, or life-threatening adverse events requiring treatment discontinuation.
- 3) When the medical judgment of the healthcare provider indicates that further participation in the series of follow-up tests could be detrimental to the patient's health or well-being.
- 4) Failure to comply with the regulations outlined in the clinical trial protocol.

If a participant is suspected to have progressed to dementia during the course of the clinical trial and they do not refuse, their participation in the trial will continue. This does not constitute a criterion for exclusion from the trial. However, if acetylcholinesterase inhibitors or memantine are subsequently added for the participant's benefit, this information should be recorded in the concomitant medication section of the case report form.

Participants can voluntarily withdraw from the clinical trial at any time for any reason. Participants who express their intention to withdraw, fail to attend scheduled visits, or otherwise fail to comply with follow-up observations may be considered as having dropped out of the trial prematurely.

### **12.2.2 Handling of Withdrawal**

- Participants who withdraw from the clinical trial due to simple mood changes will be excluded from the study population.
- If the discomfort is not due to simple mood changes but is caused by the trial itself, the underlying reason will be analyzed and attached to the case report.

## **12.3 Re-screening**

### **12.3.1 Re-screening**

Screening failure is defined as a situation where a trial participant has consented to participate in the clinical trial but cannot proceed with the trial due to reasons such as selection/exclusion criteria before randomization. Under the discretion of the Principal Investigator, screening failures can be re-screened based on the criteria outlined in the approved clinical trial protocol. Subjects who have been disqualified during the screening process may undergo re-screening only once, provided that

they provide their renewed written consent. Prior to re-screening, these subjects must provide a new informed consent, and they will be assigned a new subject identification number.

## 13. Outcome Measure, Statistical Analysis, and Interpretation

### 13.1. Outcome Measure

#### A. Primary Outcome Measure

Change in ADAS-Cog test scores after 8 weeks of rTMS stimulation and the difference in change scores at the 8-week time point.

#### B. Secondary Outcome Measure

Change in neuropsychological test scores at 4 weeks and 8 weeks after 4 weeks of rTMS stimulation, and the difference in change scores between the two groups.

the change in MRI measurements at the 4-week time point and the difference in change between the two groups

|                          | Items    | Outcome measures                                                                                                                                             |
|--------------------------|----------|--------------------------------------------------------------------------------------------------------------------------------------------------------------|
| Neuro-psychological test | CANTAB   | Change in PRM (Pattern Recognition Memory), RVP (Rapid Visual Processing), and SWM (Spatial Working Memory) scores at 4 weeks and 8 weeks after intervention |
|                          | K-MMSE   | Change in K-MMSE score at 4 weeks and 8 weeks after the intervention.                                                                                        |
|                          | K-MoCA   | Change in K-MOCA score at 4 weeks and 8 weeks after the intervention.                                                                                        |
|                          | ADAS-Cog | Change in ADAS-cog score at 4 weeks after the intervention.                                                                                                  |
|                          | CDR      | Change in CDR-SOB score at 4 weeks and 8 weeks after the intervention.                                                                                       |
|                          | COWAT    | Change in COWAR score at 4 weeks and 8 weeks after the intervention.                                                                                         |
|                          | Stroop   | Change in stroop score at 4 weeks and 8 weeks after the intervention.                                                                                        |
|                          | TMT      | Change in TMT score at 4 weeks and 8 weeks after the intervention.                                                                                           |
|                          | S-IADL   | Change in SIADL score at 4 weeks and 8 weeks after the intervention.                                                                                         |

|     |                  |                                                                                                          |
|-----|------------------|----------------------------------------------------------------------------------------------------------|
|     | K-GDS short form | Change in K-GDS short form score at 4 weeks and 8 weeks after the intervention.                          |
| MRI | DTI              | The change in fractional anisotropy (FA) values after 4 weeks                                            |
|     | Resting fMRI     | A qualitative analysis using BOLD (blood-oxygen-level-dependent) images will be conducted after 4 weeks. |

### 13.2. Statistical Analysis of the Efficacy

This study is an exploratory, investigator-driven clinical trial. Initially, instead of applying statistical analysis for clinical efficacy, the focus will be on exploring the differences in the changes of primary and secondary variables before and after the application of rTMS (or Sham coil) in the experimental and sham groups. The aim is to investigate how much difference exists and to describe these findings through exploratory research.

Additionally, for the statistical analysis of clinical efficacy, a linear mixed-effects model will be employed. This model will incorporate the intervention group, time points, and other key covariates as fixed effects. This approach will allow for the assessment of the intervention's impact over time while accounting for individual variations and potential confounding factors.

## 14. Criteria, Methods, and Reporting for Safety Evaluation, Including Adverse Events

All registered participants who underwent rTMS application in this study will be included in the safety evaluation. Participants who did not receive rTMS or for whom safety information was not collected during follow-up observations will be excluded from the analysis.

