#### 2) Secondary Outcome Measure

- 1) Study Design: Single-arm design
- 2) Allocation: Random assignment
- 3) -Compare changes in K-GDS short form and S-IADL scores between baseline, 4 weeks after rTMS stimulation, and 8 weeks after.  
-Compare changes in K-MMSE, K-MoCA, CDR-SOB, ADAS-Cog, COWAT, Stroop, TMT, RVP, SWM, PRM scores between baseline and after 4 weeks of rTMS stimulation.  
-Compare FA values in DTI analysis at 4 weeks after rTMS stimulation.  
-Examine functional network changes in resting-state fMRI at 4 weeks after rTMS stimulation.
- 4) masking: Blinded assessment by evaluators

- 1) Study Design: Parallel design
- 2) Allocation: Random assignment
- 3) Intervention Group: rTMS application group  
Control Group: Sham group (sham coil emits sound only, no rTMS stimulation)
- 4) -Compare K-MMSE, K-MoCA, CDR, ADAS-Cog, COWAT, Stroop, TMT, RVP, SWM, PRM scores between intervention and control groups after 4 weeks.  
-Compare FA values in DTI analysis between intervention and control groups at 4 weeks after.  
-Examine functional network changes in resting-state fMRI between intervention and control groups at 4 weeks after.
- 5) masking: Blinded assessment by evaluators

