## B. Trial Procedures

[figure not shown]

The study will include two groups:

- rTMS group: Actual rTMS stimulation will be administered for 4 weeks.
- Sham group: Sham stimulation (with sham coil producing sound only, no actual rTMS stimulation) will be administered for 4 weeks.

A total of 32 patients will be enrolled. They will be randomly divided into two groups:

- rTMS group (n=16): Patients receiving actual rTMS stimulation.
- Sham group (n=16): Patients receiving sham stimulation.

Both types of stimulation will be conducted for a duration of 4 weeks in all 32 patients.

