10) The acquisition of Diffusion Tensor Image and resting fMRI will be carried out simultaneously with MRI imaging (i.e., during the MRI scan). This means that any side effects associated with MRI will also apply to the acquisition of diffusion tensor image and resting fMRI. A portion of the 30-minute MRI scan will be dedicated to acquiring the diffusion tensor image and resting fMRI data. The information obtained from the fMRI will be used to create a customized 3D-printed guide for accurately positioning the TMS transducer on the patient's head for targeted treatment. This guide will ensure precise guidance for the treatment location based on the patient's individual data.

11) Any newly occurring symptoms or signs after rTMS application, as well as any worsening of underlying conditions, will be documented.

12) The presence of any adverse events will be assessed after each of the 20 sessions of rTMS stimulation.

13) If an EEG (electroencephalogram) test has been conducted within the past 6 months before the enrollment date, the results of that test can be collected and utilized as a replacement for the current study's EEG assessment.

14) If an ECG (electrocardiogram) test has been conducted within the past 6 months before the enrollment date, the results of that test can be collected and utilized as a replacement for the current study's ECG assessment.

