### 14.2 Method for Safety Evaluation

The safety is evaluated through adverse events and vital signs. All reported adverse events following rTMS application will be summarized in terms of severity and causality. The frequency and percentage of the number of participants and occurrences of adverse events will be presented in a chart. As for vital signs, continuous variables will be summarized using mean, standard deviation,

median, and range, while categorical variables will be summarized using frequency and percentage. Additionally, clinically significant results will be summarized and presented separately.

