## **14.3 Reporting adverse events**

### **14.3.1 Subjects of Evaluation**

All participants involved in the clinical trial

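### Read literally, the safety set leaves out the sham group, and it can leave out early leavers whose adverse events were already recorded

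*Protocol*

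**What the plan says.** Section 14 opens with the inclusion rule, "All registered participants who underwent rTMS application in this study will be included in the safety evaluation", and follows it with the exclusion rule, "Participants who did not receive rTMS or for whom safety information was not collected during follow-up observations will be excluded from the analysis". Section 14.2 describes the summary in the same terms: "All reported adverse events following rTMS application will be summarized in terms of severity and causality". It names no comparison between groups.

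The control condition is defined in section 9.A.2 as "sham coil emits sound only, no rTMS stimulation", and section 9.B repeats it: "Sham group: Sham stimulation (with sham coil producing sound only, no actual rTMS stimulation) will be administered for 4 weeks". Section 13.2, on efficacy, names the sham coil beside rTMS when it means both groups.

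Section 14.3.1, under the heading on reporting adverse events, gives a wider population: "All participants involved in the clinical trial".

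On collection, note 12 to the section 10 schedule says: "The presence of any adverse events will be assessed after each of the 20 sessions of rTMS stimulation". Section 10.A(13) adds a log after every session that records any adverse reaction.

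**The concern.** A safety set is normally everyone exposed to the study procedure, with the control group kept as the reference. Here the rule turns on receipt of rTMS, which the protocol says the sham group does not get. The protocol's own side-effect table calls headache and neck pain frequent and attributes syncope mostly to psychological causes rather than to the stimulation. Such events can also occur in sham sessions. Without the sham rate, a summary of the active group alone cannot separate the effect of the magnetic field from the effect of attending 20 sessions.

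The second condition makes inclusion depend on something that happens after treatment starts. If people leave because of an event and then have no follow-up safety data, the rule removes the cases that a safety analysis most needs.

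**Working it through.** **Step 1. Plan's figure.** Section 7.D gives 16 sham + 16 rTMS = 32, which agrees with section 9.B. No event rate or dropout rate is given anywhere in the protocol.

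**Step 2. Who is in the set.**
- Literal reading: rTMS received = active group only. Active ≤ 16, sham = 0, so the set is at most 16/32 = 50% of those randomised.
- Loose reading: rTMS = any session with the device. Active ≤ 16, sham ≤ 16, so the set is at most 32.
- Text for the literal reading: the sham definitions in sections 9.A.2 and 9.B, and the separate naming of the sham coil in section 13.2.
- Text for the loose reading: section 9.D (Masking) speaks of receiving and delivering rTMS where the mode may be active or sham. The rTMS application column of the section 10 schedule carries the device row for both groups. Section 14.1 refers to use of the medical device without distinguishing modes.

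**Step 3. What the follow-up condition does.** The schedule has a treatment column (Visits 4–23) and separate follow-up columns at 4 weeks (Visits 24–25) and 8 weeks (Visit 26). Section 14 does not say whether its follow-up observations are those later visits or any observation after application.
- If the later visits: a participant can have events in the session log (section 10.A(13), note 12) and still be excluded. Section 11.1(3) (persistent pain) and section 12.2.1 (serious adverse events) make harm a route out of the study. Sections 12.1.1 and 12.2.1 also foresee missed visits.
- If any observation after application: only people with no safety data at all are lost.

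**Step 4. Direction of the bias.** Let *n* be treated, *e* of them with an event, and let *k* be excluded, *m* of them with an event. The reported rate is (*e* − *m*)/(*n* − *k*). It is below *e*/*n* only when *m*/*k* > *e*/*n*, that is, when the excluded have events more often than the group as a whole, and hence more often than those who stay.

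**Step 5. Illustrations (assumed counts).**
- One event in 16, that person excluded: 1/16 = 6.25% becomes 0/15 = 0%.
- Four events in 16 (25.0%), with 1, 2, 3 or 4 of those people excluded: 3/15 = 20.0%, 2/14 = 14.3%, 1/13 = 7.7%, 0/12 = 0%.
- Four events in 16, one event-free person excluded: 4/15 = 26.7%, so the rate rises.

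**The case against.** The strongest reply is that rTMS is shorthand for the device session. Section 9.D and the schedule do use it that way, and on that reading section 14 keeps both groups. This stands as evidence of what the authors may have meant. A reader might infer that the protocol definitely discards all 16 sham participants; the documents do not support that certainty. They do support saying that the rule, followed as written, has that effect.

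A reader might also infer that anyone who has an event and stops will be removed. That goes too far. The follow-up term is undefined, section 12.1.2 says discontinued participants continue to be observed with their progress recorded, and section 10.A(14) allows additional visits. These provisions reduce the loss but do not exclude it, since missed visits are foreseen.

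Nor is a downward bias certain: step 4 shows that it depends on who leaves.

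The conflict with section 14.3.1 is softer than it looks. That section concerns reporting, and a reporting population may be wider than an analysis set. It does not change the exclusion in section 14, but the two should be aligned.

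One could add that with no events in 16 the one-sided 95% upper limit is 1 − 0.05^(1/16) = 17.1%. That reflects the size of the active group and is the same after the fix, so it does not measure this defect.

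Finally, the trial is exploratory, safety is summarised descriptively, and each event receives an individual causality assessment. It is therefore too strong to say that events cannot be attributed at all. An active-only summary still gives up the randomised reference that the trial has.

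**Conclusion.** The point holds in a qualified form. On the literal reading, the safety set is at most 16 of 32 participants and contains no sham participants, so adverse events and vital signs cannot be compared between groups. On the loose reading both groups stay, and the fault is one of wording. The text does not settle which applies.

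The follow-up condition can also drop participants with recorded events if it refers to the 4- and 8-week visits. It then understates the active-group rate if those leavers have more events than the others. The size cannot be computed from the protocol, which gives no rates; 1/16 becoming 0/15 shows how much a single case matters in a group this small. The rule is stated text that misdirects the analysis if followed, not a detail left open for a later plan.

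**What to change.** Replace the population rule in section 14 with wording such as: *The safety set comprises every participant who had at least one active or sham session, analysed by the stimulation actually received. Events recorded at any session or visit count. No one is left out because follow-up data are missing.* Analysis by stimulation received suits a coil whose mode the operator selects.

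In section 14.2, tabulate adverse events and vital signs by group. Reword section 14, section 14.2 and notes 11 and 12 of the section 10 schedule to say active or sham. The notes matter because, read as strictly as section 14, they would not require sham events to be collected. Align all of these with section 14.3.1.

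The cost is minor rewording and one extra table column. The session logs that supply the data are already part of the protocol.

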### 14.1 Criteria for Safety Evaluation

- Symptoms reported by the participant related to adverse events occurring during or after the use of the medical device.

Table. Reported side effects in high frequency rTMS [14]

| Side effects                                     | Frequency                                                                      |
|--------------------------------------------------|--------------------------------------------------------------------------------|
| Seizure                                          | In patients with epilepsy~ 1.4%
In health individuals<1%                    |
| Transient acute hypomania induction              | Possible occurrences during left prefrontal cortex stimulation.                |
| syncope                                          | Often appears due to psychological reasons rather than direct effects of rTMS. |
| Headache, localized pain, neck pain, paresthesia | Frequent                                                                       |
| Transient hearing loss                           | Possible                                                                       |
| Burns                                            | Occasionally reported                                                          |

- vital sign (blood pressure, body temperature, heart rate)

